#### Control condition: internet-delivered general psychological support

2.3.2

Participants who are randomized to the control group will receive access to brief psychoeducational content about TS/CTD in the platform in combination with general psychological support from a therapist. The materials will be divided in two chapters. Chapter 1 will cover the topics of what tics are, and the different ways stress can influence the symptoms. Chapter 2 will focus on supporting stress management and healthy lifestyle habits related to food, sleep, and physical activity. No active BT components (i.e., ERP, HRT, applied relaxation) are provided to the participants in the control group. The therapists will welcome the participants to the treatment, encourage them to engage in the treatment content and to reach out to the therapist if they have any questions. Thereafter, the therapists will only reply to the participants’ messages without taking any contact initiative themselves (unless there is an indication of severe deterioration or severe depressive symptoms or suicidal ideation requiring medical attention). The aim of the control condition is to control for basic therapist attention, relevant disorder-specific content, and the passage of time. The participants in the control group who wish to have additional help will have an opportunity to receive I-BT after the data from the first long-term follow-up (week 23 after the start of the treatment) are collected.

#### Therapists

2.3.3

The therapists will answer participants’ messages within 24 h on weekdays. The therapists will be licensed psychologists and psychologists or psychology students under supervision and with basic training in cognitive behavior therapy. All therapists will be treating participants in both conditions. The therapists will receive a half-day training in the program followed by supervision sessions every two weeks throughout the duration of the trial with an experienced therapist.

### Outcomes

2.4

If not specified otherwise, the outcome measures will be collected at pre-treatment, at week 11 counting from the start of the treatment (post-treatment, primary endpoint), week 23 (3 months after the end of the treatment), and 14 months after the treatment start (12 months after the end of the treatment) (Table 3).

**Table 3 T3:** Overview of the recruitment, treatment, and assessment points and measures.

	Enrolment	Allocation	Pre-treatment	Week 1–3	Week 4–7	Week 8–10	Week 11 (post-treatment, primary endpoint)	Week 23	14-month follow-up
Enrolment									
Eligibility screen	X								
Informed consent	X								
Allocation		X							
Treatment									
ERP				X	X	X			
Control condition				X	X	X			
Clinician-administered measures									
DSM-5 criteria for TS/CTD	X								
SCID-5	X								
MINI	X								
YGTSS	X						X	X	X
CGI-S	X						X	X	X
CGI-I							X	X	X
iiPAS					X		X		
Self-rated measures									
ATQ1	X		X	X	X	X	X	X	X
RAADS-14			X						
ASRS			X						
PUTS			X						
MADRS-S^b^	X		X	X	X		X	X	X
AUDIT	X								
DUDIT	X								
WSAS^a^			X	X	X	X	X	X	X
GTS-QoL			X				X	X	X
AQoL-6D			X				X	X	X
TIC-P			X				X	X	X
Negative effects							X	X	
Other adverse events				X	X		X	X	
CEQ					X				
WAI-SR					X				
Time spent on the programme^a^				X	X	X	X	X	X

AQoL-6D, assessment of quality of life—6 dimensions; ASRS, adult ADHD self-report scale; ATQ, adult tic questionnaire; AUDIT, alcohol use disorders identification test; CEQ, credibility and expectancy questionnaire; CGI-I, clinical general impression—improvement; CGI-S, clinical general impression—severity; DUDIT, drug use disorders identification test; ERP, exposure with response prevention; GTS-QoL, gilles de la Tourette syndrome—quality of life scale; iiPAS, internet interventions patient adherence scale; MADRS-S, montgomery—asberg depression rating scale—self-rated; MINI, the mini international neuropsychiatric interview; PUTS, premonitory urge for tics scale; RAADS-14, ritvo autism and asperger diagnostic scale; SCID-5, OCD and related disorders section of the Structured Clinical Interview for DSM-5; TIC-P, treatment inventory of costs in patients with psychiatric disorders; TS/CTD, Tourette syndrome/chronic tic disorder; WAI-SR, working alliance inventory—self-rated; WSAS, work and social adjustment scale.

^a^
Administered weekly during the 10-week treatment.

^b^
Administered at week 3 and 7.

The primary outcome measure will be the YGTSS-TTS (22), administered by a clinician blinded to the randomization condition. The raters will be psychiatrists or psychiatry residents, clinical psychologists, psychologists under training or psychology students receiving supervision. The raters will receive training in administering the YGTSS and participate in at least two test ratings with subsequent supervision before they are allowed to conduct assessments in the trial. Co-ratings will be arranged every 6 months for the active raters during the data collection period. Data on inter-rater reliability will be reported.

Secondary clinician-rated outcome measures will be the YGTSS-Impairment, as well as the Clinical Global Impression—Severity and Improvement (CGI-S and CGI-I, the latter not administered at pre-treatment) (23). The clinicians will receive training in administering the CGI that will be repeated every 6 months. Participants that are rated as “much improved” or “very much improved” on the CGI-I will be classified as treatment responders (24). If the participant keeps the responder status at subsequent follow-ups, they will be classified as long-term responders at that follow-up.

Self-rated tic-specific outcome measures will be the Adult Tic Questionnaire (ATQ) (also administered weekly) (25), the Gilles de la Tourette Syndrome—Quality of Life Scale (GTS-QoL) (26), and the Work and Social Adjustment Scale (WSAS) (27) adapted for TS/CTD by the research team. General quality of life will be measured using the Assessment of Quality of Life—6 Dimensions (AQoL-6D) (28), and these scores will be used in the health-utility analysis (see below). Symptoms of depression will be assessed using Montgomery-Asberg Depression Rating Scale—Self-report (MADRS-S) (29) (also administered at week 3 and 7). The self-reported Treatment Inventory of Costs in Patients with psychiatric disorders (TIC-P) will be administered to measure health-related costs (30).

The participants’ adherence to the treatment will be measured by their therapist using the Internet Intervention Patient Adherence Scale (iiPAS) (31) at week 6 and 11. In the ERP condition, once the Ticstimer is introduced, the participants will be asked to assess weekly how much time they have spent practicing. The participants will rate the perceived credibility of the treatments using the Credibility and Expectancy Questionnaire (CEQ) (32) at week 5. The participants will also fill out the Working Alliance Inventory—Self-Report (WAI-SR) (33) at week 5. Data on the number of sent and received messages, phone calls, and completed treatment chapters will be collected, as well as data on time spent by the therapists on supporting each participant.

The following instruments will only be administered at pre-treatment: The Mini International Neuropsychiatric Interview (M.I.N.I.) (34) and the OCD and related disorders section of the Structured Clinical Interview for DSM-5 (SCID) (35) to assess psychiatric comorbidities (clinician-administered); questions on tic symptoms following DSM-5 criteria for TS/CTD to confirm the diagnosis (clinician-administered), as well as the following self-rated measures: Premonitory Urge for Tics Scale (PUTS) (36), Alcohol Use Disorders Identification Test (AUDIT) (37), Drug Use Disorders Identification Test (DUDIT) (38), the Ritvo Autism and Asperger Diagnostic Scale (RAADS-14) (39), and the Adult ADHD Self-report Scale (ASRS) (40). Data on medication and previous psychological treatments will be collected at the baseline clinical assessment.

Negative effects will be assessed by administering a 16-item questionnaire on negative events developed by the research group at post-treatment and at week 23. Adverse events connected to worsened symptoms, suicidality, and impatient care will be measured using an additional questionnaire developed by the research group focusing specifically on whether those events have occurred, with possibility for elaboration, also administered at week 6. Spontaneously reported adverse events will be registered. Patient safety will be monitored during the recruitment procedures, by administering the MADRS and an adverse events questionnaire twice during the treatment, as well as by clinician monitoring in their contact with the participants. In case of significant deterioration, severe depressive symptoms or signs of suicidality, or in case of progression of other psychiatric disorder needing medical attention, the participant will be contacted for an additional assessment and an experienced clinician will decide on recommended future care (e. g., discontinuation of the treatment, referral to inpatient or other outpatient care).

To promote completion of follow up questionnaires, the participants will receive automatic reminders via text messages in the study platform. In case of longer measurement inactivity, study personnel will be contacting the participants via text messages or by phone.

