The primary aim of the study is to investigate whether guided internet-delivered ERP-based BT is superior to an active control condition consisting of guided internet-delivered general psychological support in reducing TS/CTD symptoms. We hypothesize that, compared to the control group, participants in the treatment group will show greater reduction in tic severity, as measured with Yale Global Tic Severity Scale - Total Tic Severity subscale (YGTSS-TTS) (22) at the primary endpoint (post treatment or week 11 after treatment start).

The secondary aim at the primary endpoint (week 11 after the start of the treatment) is to compare the two arms regarding:
(1)Tic-related impairment(2)Rates of responders(3)Self-rated tic severity(4)Symptoms of depression(5)Quality of life(6)Cost-effectivenessThe third aim is to evaluate long-term maintenance of gains. We hypothesize that the intervention condition will be superior to the control condition at week 23 after the treatment start (better response, less severe symptoms, higher quality of life) regarding all outcome measures and that the results will be maintained in the intervention group at the 14-month follow-up. The fourth aim is to evaluate the cost-effectiveness of the intervention from the healthcare organization payer perspective, the healthcare system perspective, and the societal perspective.

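### The two dedicated harms questionnaires stop at week 23, although the outcome battery is repeated at 14 months and controls may first receive I-BT after week 23

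*Protocol article*

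**What the plan says.** The Outcomes section sets a default schedule: "If not specified otherwise, the outcome measures will be collected at pre-treatment, at week 11 counting from the start of the treatment", then at week 23 and at 14 months. The harms forms are specified otherwise. For the 16-item form: "Negative effects will be assessed by administering a 16-item questionnaire on negative events developed by the research group at post-treatment and at week 23". A second questionnaire asks whether worsened symptoms, suicidality or inpatient care have occurred, "with possibility for elaboration, also administered at week 6".

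Table 3 agrees on where both forms end. The negative-effects row is marked at weeks 11 and 23. The row "Other adverse events" is marked at weeks 1–3, weeks 4–7, week 11 and week 23. Both cells are empty at 14 months. In that same column YGTSS, CGI-S, CGI-I, ATQ, MADRS-S, WSAS, GTS-QoL, AQoL-6D and TIC-P are all marked.

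The Control condition section says that controls who want further support "will have an opportunity to receive I-BT after the data from the first long-term follow-up (week 23 after the start of the treatment) are collected". The Introduction hypothesises that "the results will be maintained in the intervention group at the 14-month follow-up".

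**The concern.** The visit at 14 months takes place and most of the battery is given, but the two forms written to detect harm are left out. This is a stated schedule that the text and Table 3 share, so it is not a detail that a condensed article has merely passed over.

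Two things are at stake. First, benefit is followed to 14 months: the Introduction sets a maintenance hypothesis, and the Statistical methods section plans tests of responder and long-term responder proportions at all endpoints. Harm has no dedicated enquiry beyond week 23, so the trial cannot set long-term harms beside long-term benefit on the same footing. Secondly, the last harms forms given to controls precede any I-BT they may receive. Their answers describe the control condition only, and a second group exposed to the programme adds nothing through these forms.

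**Working it through.** **Inputs.** All come from the Protocol article, Outcomes section and Table 3, unless noted.
- Last harms forms: week 23, described as "week 23 (3 months after the end of the treatment").
- End of follow-up: "14 months after the treatment start (12 months after the end of the treatment").
- Treatment lasts 10 weeks (Interventions).
- One month = 365.25 / 12 / 7 = 4.348 weeks.

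**Step 1: reproduce the plan's own timing.** Treatment end plus three months = 10 + 3 × 4.348 = 23.0 weeks. This matches the stated week 23.

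**Step 2: the gap.** 14 × 4.348 = 60.9 weeks. 60.9 − 23 = 37.9, or about 38 weeks. 37.9 / 60.9 = 62% of follow-up.

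**Step 3: sensitivity to how the end point is counted.** Twelve months after treatment end is 12 × 4.348 = 52.2 weeks later. With treatment end at week 10, the gap is 10 + 52.2 − 23 = 39.2 weeks. With treatment end at week 11, it is 40.2 weeks. The range is 38 to 40 weeks.

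**Step 4: what is collected after week 23, by domain.**

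| Domain | Dedicated form, to week 23 | Measure at 14 months |
|---|---|---|
| Worsened symptoms | Adverse-event form | YGTSS, CGI-S, CGI-I, ATQ |
| Suicidality | Adverse-event form | MADRS-S; the plan uses the MADRS for safety monitoring during treatment |
| Inpatient care | Adverse-event form | TIC-P, collected for costing and covering use of medical resources |
| Negative effects of treatment | 16-item form | None |

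The severity scales describe the participant's state at the visit. An episode that began and resolved between week 23 and 14 months need not show in them. TIC-P comes closest to an event history, but the article gives it a costing purpose and does not state its recall window. No 14-month measure is described as asking about negative effects of treatment, or which adverse events have occurred since the last assessment.

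**Step 5: what extra exposure could add (illustration only).** If no serious event is seen among n exposed, the 95% upper bound on its risk is 1 − 0.05^(1/n). The 110 participants split 1:1 give about 55 per arm.
- n = 55 (intervention arm only): 5.3%.
- n = 82 (about half of the controls also take up I-BT): 3.6%.
- n = 110 (all controls take it up): 2.7%.

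The article does not state uptake, so the last two lines rest on assumed values. They also ignore dropout and pool randomised with self-selected, uncontrolled exposure.

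**The case against.** The strongest reply is that harm is not ignored after week 23. A reader might infer from the blank cells that nothing then asks about worsened tics, or that harm comes to light only if a participant volunteers it. The documents do not support either inference. Tic severity and change are rated by clinicians and by participants at 14 months in both arms. MADRS-S and TIC-P bear on two other domains of the adverse-event form. Spontaneous reports are registered with no stated end date. The Ethics section promises close symptom monitoring by study personnel, also with no end date, and the description of I-BT makes following up safety issues part of the therapist's role. This part of the reply stands and limits the point to the dedicated forms.

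A second reply is that the article does not describe how I-BT is delivered to or monitored in controls. That also stands: one cannot conclude that the delayed treatment is unmonitored, only that no dedicated harms form is scheduled after it in this article.

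Third, the intervention arm is asked about harms during treatment, at week 11 and at week 23. Its gap is off-treatment time, and the randomised comparison is intact. Correct, and it bears on the weight of the point. It does not answer the mismatch with the 14-month benefit claims.

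Fourth, one form with about 38 weeks of recall cannot place events before, during or after delayed I-BT, and the Ethics section says that participants who engage in another treatment are not automatically discontinued. This also stands. It is a reason to report such data without attribution, not a reason to collect none.

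**Conclusion.** The point holds as a gap in the schedule, with partial rather than absent capture. It lasts about 38 weeks, up to 40 if follow-up is counted from treatment end, which is 62% of follow-up on the 14-month count. It threatens neither the primary analysis nor the randomised harms comparison at weeks 11 and 23, and no sample-size figure depends on it. What it limits is the trial's account of long-term harms and of harms among controls who later take up I-BT.

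The conclusion rests on reading the two empty cells as intended, which the text supports, and on the 14-month visit going ahead as planned. The size of the later-exposed group is unknown, so the zero-event bounds show only what might be gained and are not estimates of what is lost. This is a cheap improvement worth making, not a flaw that undermines the trial.

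**What to change.** Add the existing 16-item negative-effects questionnaire and the existing adverse-event questionnaire to the 14-month self-rated battery in both arms, asking about the time since the last assessment. Mark both rows at 14 months in Table 3.

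Report the answers descriptively. Show controls who took up I-BT as a separate, uncontrolled group, labelled as events after the offer of I-BT and not as events caused by it.

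Apply the change to every 14-month visit still to come. The first participant was included on 8 February 2024, so the earliest such visit falls in about April 2025, and the last follow-up is preliminarily July 2026. Any visits already completed when the change takes effect should be reported as lacking these forms.

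The cost is one amendment and two short online forms at a visit that already takes place, with no extra staff or visits. The drawbacks are a few minutes of participant time and a long recall period, which will blur the dating of events and may miss mild ones.

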### Sample size

2.5

The within-group effect size in the feasibility trial was Cohen's d = 0.49 (21). As tic severity is known to fluctuate over time, we expect a certain amount of improvement in the control condition. However, we do not expect it to be as large as in the two previous ERP-based I-BT studies in children (19, 20), because the control group in those studies was much more potent. Furthermore, the participants in our previous adult pilot trial improved as much as the participants in a previous adult trial (18), but their pre-treatment tic severity was unexpectedly low, making the overall pre-to-post-treatment effects small. In the current trial, we expect the participants to have a more representative pre-treatment tic severity and their improvement to the primary endpoint is expected to be larger. In sum, we assume the between-group effect-size measured with Cohen's d to be around 0.5. With *n* = 50 participants in each group we will achieve 80% power to detect the effect of between-group Cohen's d = 0.5 (one-tailed test). A total sample size of *n* = 110 will allow for 10% drop-out rate.

### Randomization and blinding

2.6

The participants will be starting treatment in cohorts. Every time a cohort is ready to start, the online service random.org will be used to create a randomized list of the participants included into the cohort. The list will be emailed to a person not associated with the research group with the instruction to choose the following: (1) where an imaginary line dividing the cohort into two approximately equal groups should be drawn, and (2) whether the group above the line should be marked with “I” (meaning intervention) or “K” (meaning control). The outcome assessors will be blinded to the allocation of the participants, and they will be asked to guess the allocation after each assessment. The frequency of correct guesses will be reported as a measure of blinding integrity.

### Statistical methods

2.7

The significance level for all statistical tests will be *α* = 0.05. For all scale level measures, Cohen's d will be used as a measure of effect size. Odds ratios will be reported for categorical variables. Confidence intervals (95%) will be reported for all estimated measures.

The intention-to-treat approach to the analysis population will be applied in all cases unless specified otherwise. In case more than 10% of the data is missing, maximum likelihood imputations will be performed based on demographical data and the scores from the pretreatment assessment. The between-group differences at week 11 (primary endpoint) for the primary (YGTSS-TTS) and secondary outcome measures, an analysis of covariance (ANCOVA) with pre-score of the measure as covariate will be calculated. For ATQ and WSAS that are collected weekly, mixed effect models will be applied with random intercept and random slope. Chi squared tests will be calculated to explore the between-group differences in proportions of responders and long-term responders at all endpoints.

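### Missing data are handled only above a 10% trigger that equals the planned drop-out, so the primary method is settled after randomisation and up to 11 of 110 participants can leave an intention-to-treat ANCOVA; the likely bias is small

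*Protocol article*

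**What the plan says.** All of the following is from the Protocol article.

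- **Population** (2.7 Statistical methods): "The intention-to-treat approach to the analysis population will be applied in all cases unless specified otherwise".
- **Missing data** (2.7): "In case more than 10% of the data is missing, maximum likelihood imputations will be performed", with the imputation "based on demographical data and the scores from the pretreatment assessment". The section does not say what the 10% is a percentage of, and gives no handling for 10% or less.
- **Primary analysis** (2.7): for week-11 YGTSS-TTS and the secondary measures, "an analysis of covariance (ANCOVA) with pre-score of the measure as covariate will be calculated".
- **Mixed models** (2.7) are named for two self-rated measures only: "For ATQ and WSAS that are collected weekly, mixed effect models will be applied with random intercept and random slope".
- **Planned loss** (2.5 Sample size): "A total sample size of *n* = 110 will allow for 10% drop-out rate".
- **Contact during treatment**: ERP therapists follow up inactivity (2.3.1). After the welcome, control therapists answer messages "without taking any contact initiative themselves", apart from safety concerns (2.3.2).
- **Outcome collection** (2.4 Outcomes): blinded clinicians rate the YGTSS. Automatic reminders, and contact by study personnel after longer measurement inactivity, are described without distinction by arm.

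**The concern.** An ANCOVA with one post-baseline value per person cannot use anyone who lacks that value. Below the trigger nothing else is invoked, so randomised participants without a week-11 score leave an analysis labelled intention-to-treat. What is known of their course on treatment (weekly ATQ and WSAS, possibly a week-23 YGTSS) plays no part in the primary comparison.

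The threshold also sits on the planning value for drop-out. Which method produces the primary result is therefore decided by a count seen only after randomisation, and the undefined denominator leaves room to argue about that count once the data are known.

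At stake are the claim to describe the randomised population, the pre-specification of the primary method, and some bias if loss is unequal between arms and related to how participants were doing on treatment.

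This point is about the trigger and the branch beneath it. The content of the imputation model above 10% is a separate question.

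**Working it through.** **1. The plan's own figure.** Inputs from 2.5 and 2.7: d = 0.5, one-tailed α = 0.05, power 80%.

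n per arm = 2(1.645 + 0.842)² / 0.5² = 2 × 6.18 / 0.25 ≈ 49.5, so 50. Power with 50 per arm is 0.804 by the normal approximation and 0.799 by the noncentral t. 100 × 1.10 = 110. The sample size reproduces.

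**2. Where the trigger falls.** Assume the count is of participants without week-11 YGTSS-TTS out of 110.

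- 11/110 = 10.0%, not more than 10%: no imputation, and the ANCOVA uses 99 of 110.
- 12/110 = 10.9%: imputation.

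Another denominator moves the switch point but does not remove it.

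**3. Chance of crossing it.** With X ~ Binomial(110, p), P(X ≥ 12) is:

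| assumed missing rate p | P(12 or more missing) |
|---|---|
| 8% | 0.17 |
| 9% | 0.29 |
| 10% (planned) | 0.42 |
| 11% | 0.56 |
| 12% | 0.68 |

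At p = 10%, P(exactly 11 or 12) = 0.24.

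**4. Size of the bias below the trigger.** Let f be the fraction missing in an arm of 55. Let δ be the gap, in SD and after adjustment for the pre-score, between those observed and those missing, taken as equal in both arms. The shift in the contrast is about (f_ERP − f_control) × δ.

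| split of 11 losses | difference in f | shift at δ = 0.25 |
|---|---|---|
| 6 / 5 | 1/55 = 0.018 | 0.005 SD |
| 8 / 3 | 5/55 = 0.091 | 0.023 SD |
| 11 / 0 | 11/55 = 0.200 | 0.050 SD |

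Simulation supports these sizes. Its inputs are all assumed: 55 per arm, pre/post correlation 0.6, late ATQ with week-11 YGTSS 0.6, and missingness more likely with worse late ATQ (log-weight 0.5 to 1.0 per SD). The correlation of pre-score with late ATQ was set at 0.5, 0.6 or lower. The complete-case ANCOVA was biased by:

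- about 0.01 SD or less at 6/5;
- about 0.01 to 0.035 SD at 8/3;
- about 0.03 to 0.07 SD at 11/0.

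The lower ends go with weaker selection and a pre-score that predicts late ATQ better. The sign follows the arm that loses more: benefit is overstated if ERP does and understated if control does.

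For scale, the standard error with 99 analysed is about √(1 − 0.6²) × 2/√99 = 0.8 × 0.201 = 0.16 SD. So 0.035 is about 0.2 of a standard error and 0.07 about 0.4.

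A likelihood analysis that used the late ATQ averaged 0.50 at a true 0.50 in every split, with an equal or slightly smaller standard error. That is expected, because missingness was generated from the late ATQ. It shows what the collected data can correct, not protection against every mechanism.

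**5. Do the two branches differ?** If missing week-11 scores are filled with their expected value from arm and pre-score, the ANCOVA point estimate is the same as in complete cases. The branches separate only if the imputation leaves out arm (about 0.45 instead of 0.50 at a 6/5 split) or adds on-treatment scores.

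**The case against.** **The switch may change little.** ANCOVA on complete cases is already valid when missingness depends only on arm and pre-score, and imputation from those two gives the same point estimate (step 5). This stands. A reader might infer from the 0.42 that the primary result is a coin toss. It is the method that is close to a coin toss. How far the answer moves depends mainly on what the imputation model contains.

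**The large bias figures need extreme inputs.** A reader might take a bias near 15% of d = 0.5, or one-tailed rejection near 12% under no effect, as the expected harm. Both need all 11 losses in one arm, strong selection, and a weak correlation between pre-score and late ATQ. If the arms lose participants equally, an 11/0 split in either direction has probability 2 × C(55,11)/C(110,11) = 0.0006. None of these inputs is in the documents. This stands.

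**Unequal loss is not shown.** It is tempting to conclude that controls will be lost more often because their therapists do not initiate contact. But reminders and personnel contact are not described as differing by arm, raters are blinded, and controls are offered I-BT only after the week-23 data, which is a reason to stay. Unequal loss is possible, not established.

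**The article never calls the lower branch complete-case, and an analysis plan may fill the gap.** Correct as to wording: the exclusion is inferred from the model named and from the absence of any other handling. But the article itself fixes the trigger, and an analysis plan that follows it inherits the trigger. That part is a stated rule, not an omission.

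**ATQ and WSAS are not discarded.** True: they have their own mixed models. They simply do not inform the primary comparison.

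**Conclusion.** The point holds as a defect of pre-specification with a modest numerical consequence. Section 2.7 ties the handling of missing data to a percentage known only after randomisation, leaves its denominator open, and sets it at the planned drop-out. Below it, the named ANCOVA omits up to 11 of 110 randomised participants despite the intention-to-treat promise.

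The 11-to-12 switch and the 0.42 assume that the count is of missing week-11 YGTSS-TTS scores and that each participant has an independent 10% chance of a missing score. The bias sizes in step 4 are conditional on correlations, selection strength and splits that the documents do not give. At a plausible split they are a small fraction of a standard error.

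The documents do not support saying that the primary result will be materially biased, or that its direction can be predicted. The change is still worth making: the rule is easily avoided and the data for a better one are already scheduled.

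**What to change.** Delete the 10% trigger. Before analysis starts, state that week-11 YGTSS-TTS is analysed in all randomised participants, whatever the amount missing, by one of:

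- a likelihood-based, baseline-adjusted model with arm by visit, using the week-23 YGTSS and the on-treatment ATQ as auxiliary information, with the week-11 contrast as primary; or
- an equivalent multiple imputation that includes arm and on-treatment scores.

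Apply the same rule to the other week-11 outcomes (for MADRS-S, include its week 3 and week 7 scores). Keep the complete-case ANCOVA as a sensitivity analysis.

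The week-23 YGTSS is usable for this because controls are offered I-BT only after it is collected. With nothing missing, the week-11 contrast is essentially the planned ANCOVA. The cost is revised wording and slightly more modelling, with no new data and no more participants. Section 2.1 already provides for posting modifications on the two registries.
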